**Table 3 Tab3:**
[figure not shown]
Schedule of events

*t*_0_ additional research clinic appointment *t*_1_ first physiotherapy treatment clinic appointment

Mean values and confidence intervals of the secondary outcomes (see Table 4) will be calculated if the data are normally distributed (this will be assessed using a combined test of skewness and kurtosis). If the data are not normally distributed, medians and interquartile ranges will be reported. The responsiveness of the different outcome measures will be compared, by calculating the treatment effect in the intervention group.

**Table 4 Tab4:** Outcome measures and time-points

Outcome measure	Baseline	6 weeks	3 months	6 months
Numerical rating scale of pain on gripping	X	X	X	X
Patient-rated tennis elbow evaluation (PRTEE) [15]	X	X	X	X
Tampa scale of kinesiophobia (TSK-11) [16]	X	X	X	X
Pain self-efficacy questionnaire (PSEQ) [17]	X	X	X	X
EQ 5D5L [18]	X	X	X	X
Pain-free grip strength (lbs)	OPTimisE group X	OPTimisE group X	OPTimisE group X	OPTimisE group X
	Usual care group X	Usual care group	Usual care group	Usual care group X
Maximum grip strength (lbs)	OPTimisE group X	OPTimisE group X	OPTimisE group X	OPTimisE group X
	Usual care group X	Usual care group	Usual care group	Usual care group X
Global perceived effect (GPE-11) [19]		X	X	X
Exercise adherence rating scale (EARS) [20]		X	X	X

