## Introduction

### Background and rationale

Tennis elbow, also known as lateral elbow tendinopathy, is a musculoskeletal condition that usually affects people in middle age and often affects an individual’s ability to work [1, 2]. In 2012, absenteeism from work due to tennis elbow cost the UK economy £27 M [3]. Common risk factors for onset have been identified as repetitive handling of heavy loads, forearm rotating motions, strong gripping force and working postures that combine force or load handling with raised arms [4]. Whilst the condition is self-limiting for many patients, 8.5–17% of individuals will have persistent symptoms, lasting more than 12 months [2, 5, 6]. Physiotherapy is recommended, but research has shown that physiotherapy treatment for tennis elbow varies widely and is suboptimal [7, 8]. In order to improve the physiotherapy treatment for people with tennis elbow, we recently developed an optimised physiotherapy treatment package by triangulating the best available research evidence, with consensus from UK physiotherapists with a special interest in tennis elbow, physiotherapy service managers and patient representatives, to ensure the intervention designed was acceptable to all stakeholders. A detailed description of this treatment package and how it was determined can be found in the open-access intervention development paper [9].

Improved physiotherapy provision for patients with tennis elbow has the potential to reduce pain, improve quality of life, reduce time off work and reduce the number of patients developing persistent symptoms. When physiotherapy fails to help, the usual pathway involves costly alternative treatments such as injections (of various types, e.g. autologous blood/platelet-rich plasma/corticosteroid/sodium hyaluronate) or surgery, but there is limited evidence for the effectiveness of these procedures [10, 11]. Surgery, however, is on the rise, for example in the USA there was a threefold increase between 2000 and 2011 [2]. In England, 2845 surgeries were performed in 2019/2020 at a cost of £1086 per procedure (total £3.1 million). If physiotherapy can be improved such that more patients with tennis elbow benefit, then fewer patients may subsequently require injections and surgery with associated cost-savings.

The newly designed optimised physiotherapy treatment package is therefore ready for feasibility and pilot trial testing, prior to conducting the main randomised controlled trial (RCT).

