### Sample size

The pilot and feasibility RCT will recruit up to 50 participants or for a maximum of 12 months across three sites. These limits were a condition stipulated by the funder. The nested qualitative study will recruit until data saturation, estimated as up to 25 participants (approximately 16 patients and 9 treating physiotherapists).

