### Assignment of interventions

#### Allocation sequence generation

Patients will be randomised in a 1:1 allocation (in mixed blocks) stratified by site using an online randomisation service provided by the CTU. Mixed blocks are required to reduce the predictability of the randomisation allocations.

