The physical measures of maximum grip strength and pain-free grip strength will also be reported by patients using the OPTimisE Follow-up Questionnaire. Patients randomised to the OPTimisE intervention will be given a Squegg device to take home at their initial research visit with an information sheet on how to use it. The OPTimisE Follow-up Questionnaire will prompt the patients to use the Squegg device and document three measures each of maximum grip strength and pain-free grip strength. Patients in the usual physiotherapy group will be sent a Squegg device at 6 months. As the device can be used for grip strength training and is not provided as part of usual physiotherapy care, it will only be used at the 6-month time-point for patients in the usual physiotherapy group, to avoid intervention contamination.

Fidelity of the optimised physiotherapy intervention will be measured retrospectively by reviewing the CRF data to establish whether the treatments provided matched the pre-defined protocol. Fidelity will be calculated as a percentage based upon the number of applicable treatment items delivered. Any additional interventions will be noted and discussed in the final data analysis and report. Similarly, CRF data will be used to review the treatment of patients receiving usual physiotherapy to assess for key differences and similarities between the interventions and determine whether there is contamination between the interventions. Adherence to treatment will be measured in both treatment arms using a patient-reported exercise diary that is reviewed by the treating physiotherapist at each session and returned to the chief investigator by the patient after 3 months, via a stamped addressed envelope. Additionally, the 6-week, 3- and 6-month outcome questionnaires will include the Exercise Adherence Rating Scale [20]. Participants will receive a £20 voucher after completing all of the study questionnaires at 6 months.

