Quantitative data analysis will be descriptive. This feasibility study aims to provide estimates of the consent, intervention fidelity, follow-up and outcome measure completion rates to inform a future main trial. By including 50 participants, we will be able to estimate a consent rate of 25% with a 95% confidence interval of (19%, 31%), an intervention fidelity of 60% with a 95% confidence interval of (46%, 74%) and a follow-up rate and outcome measure completion rate of 70% with a 95% confidence interval of (57%, 83%).Consent rate — measured as a percentage of eligible patients approached to participateIntervention fidelity in the intervention group — measured using CRF data. Fidelity to the intervention will be defined by delivery of at least 6 of the 12 prescribed advice/education topics, evidence of exercise prescription and progression in line with the protocol and provision of an elbow clasp splint. Results will be expressed as a percentage of the patients in the intervention group who received treatment assessed as being faithful to the protocol.Follow-up rate in the intervention group — the actual number of visits (excluding the baseline visit) divided by the maximum number of possible visitsOutcome measure completion rate at 6 months — measured as a percentage of outcome measures completed across both the intervention and usual care groups

If any of the above feasibility outcomes are rated red (do not proceed) as per Table 2, then a future main trial will not be feasible. If any outcomes are rated amber (proceed with changes), but without any red, then a future main trial may be feasible with changes to the protocol. If all outcomes are rated green (proceed), then a main trial is feasible.

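### The responsiveness analysis mislabels one-arm change from baseline as a treatment effect and leaves out usual-care data that would roughly double the usable sample

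*Protocol article*

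**What the plan says.** Under Outcomes, the protocol article lists a responsiveness analysis among the secondary outcomes. The method is one sentence in Statistical methods, just before Table 4: "The responsiveness of the different outcome measures will be compared, by calculating the treatment effect in the intervention group". It names no index, standardiser, time-point or anchor.

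Other parts of the article bear on this:

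- **Size and allocation.** Sample size: "The pilot and feasibility RCT will recruit up to 50 participants or for a maximum of 12 months across three sites". Allocation sequence generation: "Patients will be randomised in a 1:1 allocation (in mixed blocks) stratified by site".
- **Completion.** Statistical methods plans around a 70% outcome completion rate.
- **Data available (Table 4).** Five patient-reported measures (pain on gripping, PRTEE, TSK-11, PSEQ, EQ-5D-5L) are scheduled at baseline, 6 weeks, 3 months and 6 months, with no difference between arms. The two grip measures, in pounds, are taken at all four points in the intervention arm but only at baseline and 6 months in usual care. GPE-11 and EARS have no baseline.
- **Reason for the grip gap.** Data collection methods says of the grip device that "it will only be used at the 6-month time-point for patients in the usual physiotherapy group, to avoid intervention contamination".
- **Status.** "Quantitative data analysis will be descriptive", and the red/amber/green rule uses only the four primary feasibility outcomes.

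**The concern.** Two things are fixed badly, and a third is left open.

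1. **The label.** Inside one randomised arm the only quantity available is change from baseline. The Background says of tennis elbow: "Whilst the condition is self-limiting for many patients". That change therefore contains natural recovery as well as any benefit of the package, and a report that followed the protocol's wording would present it as an effect of treatment.
2. **The population.** Responsiveness asks whether an instrument registers change when patients change. A usual-care patient who improves, or does not, informs that question as well as an intervention patient does. For the five patient-reported measures, and for grip at 6 months, the article gives no reason to leave out half the trial.
3. **The metric.** The sentence promises a comparison between a pain rating, questionnaire scores and pounds of force, but names no common scale on which to make it.

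At stake are the precision of the comparison and the wording of the eventual report.

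**Working it through.** The article states no figure for responsiveness, so there is none to reproduce. Its planning interval for completion does reproduce at n = 50: 0.70 ± 1.96 × √(0.70 × 0.30 / 50) = 57.3% to 82.7%, against the stated 57% to 83%. The 70% is therefore taken as the planning value.

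**Patients available**
- Intervention arm at 1:1: 50 / 2 = 25. At 70% completion: 25 × 0.70 = 17.5, so about 17–18.
- Both arms: 50 × 0.70 = 35.

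**Precision of a standardised response mean (SRM = mean change / SD of change)**

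The large-sample formula is SE = √(1/n + SRM²/(2n)), and the 95% half-width is 1.96 × SE. The SRM is an assumption, because the article gives none. For SRM = 0.8, 1 + 0.8²/2 = 1.32.
- n = 17.5: 1.96 × √(1.32 / 17.5) = 0.54
- n = 35: 1.96 × √(1.32 / 35) = 0.38
- With full completion, n = 25 gives 0.45 and n = 50 gives 0.32.

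The ratio is √2 = 1.41 whatever the SRM, so one-arm intervals are about 41% wider. Across assumed SRMs of 0.5 to 1.0 the half-width runs from 0.49 to 0.57 at n = 18, and from 0.35 to 0.41 at n = 35.

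**Chance of ranking two measures correctly by SRM**

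This comes from a simulation with 20,000 replicates per setting, both measures in the same patients, and an assumed correlation of changes of 0.5 to 0.7.

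| Assumed true SRMs | n = 18 | n = 35 |
|---|---|---|
| 0.8 and 0.6 | 0.77–0.82 | 0.85–0.90 |
| 0.8 and 0.5 | 0.86–0.91 | 0.94–0.97 |

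**Why a common metric matters**

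Take two measures with assumed mean changes of 2 (SD 2) and 15 (SD 20). Raw change puts the second ahead (15 against 2). SRM puts the first ahead (2/2 = 1.0 against 15/20 = 0.75). The order depends on the metric.

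**The case against.** The strongest defence is that within-group change is an accepted basis for internal responsiveness and needs no control arm. On that view the sentence is only loosely worded, and the index may sit in a fuller document that is not shown. Much of this stands:

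- A reader might infer that the measures will be compared in raw units. The article does not say so; it is silent on scaling. The missing index alone would be a weak point.
- A reader might infer that a one-arm analysis cannot rank the measures. It can, if change is standardised: the table above shows a usable, though less certain, ranking at n = 18.
- A reader might infer that natural recovery biases the responsiveness comparison. It does not, because recovery is real change that a responsive instrument should register, and an index pooled over both arms contains it too. Natural recovery matters only if the figure is read as an effect of treatment.
- A reader might suppose that this analysis will select the main trial's primary outcome. The article does not say so.

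The design also gives a partial reason for the restriction. Only the intervention arm has grip at 6 weeks and 3 months, so only there can grip and the questionnaires be compared in the same patients at those visits. That reason does not reach the five patient-reported measures compared among themselves, or any measure at 6 months.

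Finally, the 41% is simply the cost of halving any sample, and the interval for a single SRM is not the precision of a paired comparison between two. The ranking probabilities address the paired comparison directly, and the loss there is smaller.

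**Conclusion.** The point holds in a limited form. The sentence names a quantity that one arm cannot supply, and it restricts the analysis to about half the usable patients without a reason that covers most of the measures. Neither defect would be cured by a later document that merely added an index.

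At 70% completion the loss is about 17–18 patients instead of 35, with intervals about 41% wider. For assumed SRMs of 0.8 and 0.6, the chance of a correct ranking is 0.77–0.82 instead of 0.85–0.90. These figures assume full recruitment to 50, equal completion in both arms, 70% completion at the visit analysed, and a similar SRM in each arm. The SRMs and correlations are not from the article.

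The impact is modest: a descriptive secondary outcome with no part in the progression rule. The documents do not support the stronger conclusion that the analysis is unable to rank the measures or is meant as a test of efficacy.

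**What to change.** Replace the sentence with wording to this effect: for each measure with a baseline (pain on gripping, PRTEE, TSK-11, PSEQ, EQ-5D-5L, pain-free and maximum grip), responsiveness will be summarised by a standardised within-person change index, such as the standardised response mean with 95% CI, at each stated follow-up. Both arms will be used wherever both are measured. Grip at 6 weeks and 3 months will use the intervention arm only and be labelled as such.

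State that these figures are change from baseline and not estimates of treatment effect. State also that GPE-11 and EARS, which have no baseline, will not be ranked as change scores. GPE-11 may serve as an external anchor at each follow-up; that is an option and not a correction.

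The cost is a sentence or two of analysis wording. No new data, visits or patients are needed.

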### Data monitoring and auditing

The site PIs must ensure that source documents and other documentation for this study are made available to study monitors, the REC or regulatory authority inspectors. Authorised representatives of the sponsor will visit the participating sites on two occasions to conduct audits/inspections.

### Harms

All adverse events (AEs) and serious adverse events (SAEs) will be recorded and reviewed from the time of written informed consent until 6 months following the first intervention.

All AEs and SAEs occurring during the duration of the study must be recorded by the site PI and sent to the CI within 48 h for review.

All related and unexpected SAEs must be reported by the CI using the ‘non-CTIMP safety report to REC form’ from the HRA website. The completed form should be submitted to the sponsor and REC within 15 days of the CI becoming aware of the event. Safety information will be reviewed during trial management group meetings.

## Discussion

This study will determine the feasibility of a new optimised physiotherapy treatment package for people with tennis elbow and pilot the processes for a future fully powered RCT. In the longer term, this treatment package may provide superior clinical outcomes for patients, in terms of pain and quality of life, and be more cost-effective for the health service.

The study is designed to be pragmatic and deliverable in a primary care setting. For this reason, the inclusion/exclusion criteria require no additional imaging or specialist assessment, and the usual care arm has not been standardised. The components of usual care and the OPTimisE treatment protocol that are delivered in practice will be documented as described in the ‘Data collection methods’ section. Subsequently, one of the feasibility outcomes is to assess the content of the usual care treatments given, compared to the OPTimisE treatment, to decide whether they are sufficiently different.

The optimised intervention design was based upon the principles underpinning the development of complex healthcare interventions [30], combining the best available evidence (acknowledging that this may not have all been high quality due to the limitations of the evidence base) and the input of relevant stakeholders. These included expert clinicians, service managers and patients who had experienced tennis elbow. One of the greatest limitations of the evidence base related to physiotherapy for this patient population is the lack of studies with follow-up over 3 months. Given the importance of longer-term follow-up in this persistent and/or recurrent musculoskeletal condition, it is important that we are confident that longer-term follow-up is feasible, hence the selection of the 6-month time-point as a primary outcome.

## Data Availability

Data sharing is not applicable to this article as no datasets were generated or analysed during the current study. Materials will not be made available until the completion of a future main trial, if applicable.

## Abbreviations

AE: Adverse event
CI: Chief investigator
CRF: Case report form
GCP: Good clinical practice
ISF: Investigator site file
ISRCTN: International Standard Randomised Controlled Trial Number
NHS: National Health Service
PI: Principal investigator
PIS: Participant information sheet
PPIE: Patient and public involvement and engagement
RCT: Randomised controlled trial
REC: Research ethics committee
SAE: Serious adverse event
